## Abstract

**Background:**

The continual development and implementation of effective digital interventions is one important strategy that may serve to bridge the well-known treatment gap related to problematic alcohol use. Research suggests that clinician guidance, provided in different ways during the digital intervention (i.e., written weekly messages, phone calls etc.), can boost intervention engagement and effects. *Digital psychological self-care* (DPSC) is a new delivery format wherein an unguided digital intervention is provided within the framework of a structured care process that includes initial clinical assessment and follow-up interviews. In a recent feasibility study, a DPSC intervention for problematic alcohol use, ALVA, provided without any extra guidance, was found safe and credible and to have promising within-group effects on alcohol consumption. The aim of the current study is to gather information on the effects and efficiency of different forms of guidance added to ALVA, in order to optimize the intervention.

**Methods:**

This protocol describes a randomized factorial trial where the effects of two different ways of providing guidance (mid-treatment interview, weekly written messages, respectively) in DPSC for problematic alcohol use are investigated. Optimization criteria will be applied to the results regarding how effective the intervention is at reducing alcohol consumption measured by the number of standard drinks per week together with the clinician time spent on guidance.

**Discussion:**

This study will investigate the added benefit of different forms of guidance to DPSC for problematic alcohol use. These added effects will be compared to the added cost of guidance, according to pre-defined optimization criteria.

**Trial registration:**

Clinicaltrials.gov: NCT05649982. Registered on 06 December 2022. Prospectively registered.

## Administrative information

Note: the numbers in curly brackets in this protocol refer to SPIRIT checklist item numbers. The order of the items has been modified to group similar items (see http://www.equator-network.org/reporting-guidelines/spirit-2013-statement-defining-standard-protocol-items-for-clinical-trials/).

## Introduction

### Background and rationale {6a}

Although alcohol problems are widespread and constitute a major burden on global health [1], only one in six seek help [2]. Digital interventions for alcohol problems are effective in reducing alcohol consumption and could serve to bridge this treatment gap [3]. In the largest meta-analysis conducted to date, guidance from a therapist or coach was found to boost effects of digital interventions for alcohol problems [4]. Guidance usually means that some sort of human contact is provided to the user. However, the way that the contact is provided differs in studies. The most common way guidance is provided in digital interventions is through weekly written messages exchanged on the digital platform on which the intervention is provided [5]. Other forms of guidance include synchronous chat messages [6], phone calls [7], and face-to-face sessions [8]. Although the meta-analysis from 2018 mentioned above found guidance to boost effects, added effects of guidance have been absent in some recent trials [5, 9–11]. Furthermore, a recent study showed that a guided digital alcohol intervention was non-inferior to traditional face-to-face cognitive behavioral therapy, when provided in a routine clinical setting [12].

### Digital psychological self-care—a new delivery format

Digital psychological self-care (DPSC) is a new proposed delivery format wherein an essentially self-guided digital intervention is provided within the framework of a structured care process that includes an initial clinical assessment interview with a clinician and one or several follow-up interviews [13]. The efficacy of well-designed self-guided digital interventions in depression and anxiety has in some studies been shown to be comparable to digital interventions with therapist guidance [14, 15]. Crucial for the improvement, however, seems to be a clear clinical process that employs clinical assessments and follow-up interviews, some form of clinical monitoring during the treatment, automated written support, and a material of high quality designed for the user to easily be able to guide themselves through the intervention [14]. The concept of DPSC is presented in a 2023 paper by [name] and colleagues [16].

We recently conducted a small feasibility study (*n* = 36) on a basic version of DPSC for problematic alcohol use named ALVA [13]. We found not only that the intervention was safe and credible but also that it rendered a high degree of use. In terms of effects, participants reduced their alcohol consumption from 22.6 standard drinks preceding week before the digital intervention to 10.6 standard drinks after the intervention (Hedge’s g intra-group = 0.85) and 12.7 standard drinks at a 3-month follow-up (Hedge’s g intra group = 0.70). The clinicians in the study spent less than 1 h on average per participant, time which was mainly spent on the initial clinical assessment interview and the post-intervention interview [13]. There was also a follow-up interview in the feasibility study, but this was not an essential part of the DPSC concept.

For the study described in this protocol, we propose that the basic version of DPSC for problematic alcohol use should include the following:An initial clinical assessment interview with a clinician who informs about DPSC and refers the client to appropriate health care services should DPSC be deemed not appropriateA digital intervention based on evidence-based theory with high quality texts, illustrations, exercises, patient narratives, automated written support, and interfacesProvision of immediate technical support for the client in the event of practical problems when interacting with the digital interventionA clear routine for monitoring the clients’ weekly self-assessments of alcohol consumption and symptom levels, including indications of suicidal ideationPossibility for clients to flag themselves in the event of a crisis or problem, which will lead to immediate contact with a clinician. When in doubt, DPSC for the client should be reconsideredA post-intervention interview where the client is asked about experiences and where the need for additional help is investigated

We also propose that 1 h of clinician-time per participant would signal high scalability and that it would be easy to communicate to health care providers that the intervention would be relatively easy to implement.

### Objectives {7}

The objective is to gather information on the effects and efficiency of different forms of guidance added to the basic version of digital psychological self-care for problematic alcohol use (ALVA) as tested in the earlier study, in order to optimize [17] the intervention for a future randomized controlled trial (RCT).

### Research questions

What are the main and interaction effects of the two guidance forms investigated (i.e., mid-treatment phone call, weekly written messages) on alcohol consumption, immediately after the intervention and up to 12 months after the intervention?Which combination of guidance forms is most efficient (i.e., renders the greatest effects on alcohol consumption per additional cost in the form of incremental resource consumption measured by clinician time), immediately after the intervention and up to 12 months after the intervention?Which (combination of) guidance form(s) gives the best effects on alcohol consumption given a set limit of 1 h of clinician time per participant, immediately after the intervention and up to 12 months after the intervention?

### Trial design {8}

The purpose of an optimization trial and the corresponding phase within the framework of the Multiphase Optimization Strategy is to provide the information needed to make decisions about which components to select for the optimized intervention, which will later be tested in a classic RCT [17]. The framework is exploratory and follows a decision-priority perspective, in contrast to the conclusion-priority perspective of a RCT. Although scientific conclusions are of interest, the top priority in a decision-priority perspective is to make practical decisions about which components and component-levels to select [17]. The current protocol describes a randomized factorial optimization trial [18] where the added effects of two different forms of guidance (a mid-treatment phone call interview and weekly written guidance) to the basic version of ALVA will be investigated. Optimization criteria [17] will include both additional effects on alcohol consumption and associated consumption of clinician time. The two two-level factors will result in four experimental conditions with an allocation of 1:1:1:1.

## Methods: participants, interventions, and outcomes

### Study setting {9}

The study will be conducted at the research clinic at the Centre for Psychiatry Research, Stockholm Health Care Services, and Karolinska Institutet, Sweden, in cooperation with the Addiction eClinic at the Stockholm Centre for Dependency Disorders, Sweden. Participants will be recruited nationally in Sweden via advertisements on the patient community and support website Alkoholhjalpen.se as well as through search engines and social media. The participants log in to the intervention website at egenvard.webcbt.se.

### Eligibility criteria {10}

Eligibility is both based on the screening (certain cut-off scores) and determined in the interview by the interviewer in a clinical manner. To be included in the trial, participants must (a) be ≥ 18 years, (b) have regular Internet access, and (c) score 8 points or more for men and 6 points or more for women on the Alcohol Use Disorders Identification Test (AUDIT) [19]. Potential participants will be excluded from the trial if they display (a) insufficient knowledge of Swedish, (b) reading and/or writing difficulties to the extent that it makes it difficult to participate in the intervention, (c) other ongoing psychological treatment with a content similar to that in the current study, (d) high suicide risk based on the clinical assessment interview, or (e) other urgent need for more intensive psychiatric or addiction care, based on the clinical assessment interview. Potential participants excluded will be referred to, or informed about, more appropriate care options in their regional area and condition-related area.

### Who will take informed consent? {26a}

All participants will receive detailed written information about the study and provide informed consent digitally on the study platform BASS when applying for the study. Online informed consent to participate will be obtained from all participants.

### Additional consent provisions for collection and use of participant data and biological specimens {26b}

There will be no additional consent for ancillary studies.

### Interventions

#### Explanation for the choice of comparators {6b}

The experimental factors are weekly written guidance and/or a mid-treatment interview, added to the basic version of ALVA. As stated above in the “Background and rationale {6a}” section, the existent literature is inconsistent on the added effect of including weekly written guidance in digital alcohol interventions, with one meta-analysis claiming that guidance boosts effects on alcohol consumption [4], while recent trials have failed to demonstrate such added effects of guidance [5, 9–11]. Written guidance consumes around 15 min clinician time per participant and week in the study of the earlier mentioned comprehensive intervention [5]. An added extra interview by phone could also boost engagement and effects, especially for participants in risk of treatment failure [20]. The basic version of ALVA (including two phone interviews) includes the participant setting new goals for alcohol consumption mid-treatment; guidance in the form of an extra phone interview may help with this potentially difficult task.

#### Intervention description {11a}

The intervention, ALVA, consists of techniques from cognitive behavioral therapy (CBT) and relapse prevention (see Table 1) given during 8 weeks. The intervention is centered around the alcohol diary. The alcohol diary guides participants to set goals for their alcohol consumption for 4 weeks at a time. Every morning, a text-message reminds the participant to log in and register the previous day’s consumption in the alcohol diary. The alcohol-related goals will be defined in three ways:

**Table 1 Tab1:** The content of ALVA

Component	Description
Daily alcohol diary	The digital tool for goal setting and daily registration of standardized drinks. Goal fulfillment is calculated automatically and provided back to the user with along with a visual presentation
Weekly module 1	Psychoeducation regarding alcohol and alcohol problems, reasons to change, and goal setting. Introduction of patient narratives and instructions on how to use the alcohol diary. Summary of important strategies more comprehensively introduced in weeks 2–4
Weekly module 2	Identify risk situations and strategies for handling them
Weekly module 3	Refusal skills and strategies for drinking moderately
Weekly module 4	Strategies for scheduling alternative activities, maintaining progress, and relapse prevention
Weekly module 5	Evaluate progress and set a new goal for the next 4 weeks
Weekly module 6	Encouragement to continue using the alcohol diary and strategies. New patient narrative texts
Weekly module 7	Encouragement to continue using the alcohol diary and strategies. New patient narrative texts
Weekly module 8	Encouragement to continue using the alcohol diary and strategies. New patient narrative texts
Maintenance plan	Construct a long-term maintenance plan and advice on relapse prevention

Number of standardized drinks per dayNumber of standardized drinks per weekNumber of abstinent days per week

Additional exercises include dealing with cravings, refusal skills, and finding alternative activities. After the end of the intervention, a telephone interview will be conducted where the participant will receive feedback regarding their work with the exercises and the alcohol diary. The feedback is intended to act as a motivation to continue to work with the exercises after the intervention’s 8 weeks. For a more detailed description of the basic version of the intervention, see the previous study [13]. The experimental additions to the basic version of ALVA are detailed below.

The experimental factors are as follows:

Factor 1. Weekly guidance: Written guidance similar to more comprehensive guided interventions [5] aiming at a maximum of 15 min a week per participantFactor 2. Mid-treatment interview: Focus on goal fulfillment and setting of a new 4-week goal, motivation and encouragement to continue adhere to the program, aiming at around 20 to 30 min per participant

The two experimental factors result in four different combinations (Table 2).

**Table 2 Tab2:** Factorial trial design with target sample per group

		Factor 2: Mid-treatment phone call		
		Yes	No	Total
Factor 1: Weekly written guidance	Yes	75	75	150
	No	75	75	150
Total		150	150	300

#### Criteria for discontinuing or modifying allocated interventions {11b}

Since the experimental factors are related to support, all extra support given to a participant could be said to slightly alter the allocated interventions. The suicide ideation item from self-rated MADRS-S [21] will alert the clinician monitoring the intervention if rated 4 out of 6 or over. The clinician will contact participants with suicidal ideation, or who describes severe withdrawal symptoms, by phone. This time will be measured as clinician time. There is also a possibility for all participants to alert the clinician within the system to be contacted by the study administration for technical support. All time spent on extra support for a participant will be registered. The intervention can be discontinued based on participant request, if it appears to lead to serious adverse events, or if the participant requires medical care incompatible with the intervention provided in the trial.

#### Strategies to improve adherence to interventions {11c}

Automatic text-message reminders to use the alcohol diary will be administered daily. There will also be separate reminders for self-rated assessments. If a participant is a week late with an assessment, the study administration may make a short call to the participant as a reminder. All time spent on calls will be registered.

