#### Outcomes {12}

Measurements will be made at registration (screening), before (week 0), during (week 4), and after the 8-week intervention (primary end-point, week 8), as well as at a 3-month follow-up (FU3), 6-month follow-up (FU6), and lastly at a 12-month follow-up (FU12). Measurements will take place in the form of self-assessment surveys via the secure digital treatment platform and supplemented with interview data from telephone interviews at week 0, week 8, and FU6. If there are sufficient resources available, a telephone interview may also be done at FU12.

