#### Implementation {16c}

The study administrators (MK, CS, and other clinical psychologists or psychology students with basic training in psychotherapy) will enroll participants. The allocation sequence will then be generated by a person blinded to the participants and who is not otherwise involved with the study. The study administrators will then assign the participants to the intervention groups in the digital platform according to the allocation sequence.

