### Assignment of interventions: blinding

#### Who will be blinded {17a}

There will be no blinding of participants, care providers, or assessors, but to minimize placebo/nocebo effects, the information to participants is that all participants will receive the active intervention with only some differences in added guidance. The assigned mode of added guidance will be explained to the participant after randomization by the study administration and within the intervention. The main outcomes are self-rated by the participants. The data analysist will be blinded.

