### Data collection and management

#### Plans for assessment and collection of outcomes {18a}

Self-rated assessments will be made at registration (screening), before (week 0), during (week 4), after the 8-week intervention (week 8), at a 3-month follow-up (FU3), 6-month follow-up (FU6), and lastly at a 12-month follow-up (FU12). Telephone interviews will be made by the study administrators at week 0, week 8, and FU6. If there are sufficient resources available, a telephone interview may also be done at FU12.

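### Study staff who know the allocation may choose whom to phone about a late assessment, in a trial where one factor is itself a mid-treatment phone call

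*Protocol article*

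**What the plan says.** The rule is in Strategies to improve adherence to interventions {11c}: "If a participant is a week late with an assessment, the study administration may make a short call to the participant as a reminder". The only accompanying control is that "All time spent on calls will be registered". Section {11c} also provides automatic daily text messages for the diary and separate reminders for self-ratings.

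Other sections bear on it:

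- **When assessments fall.** Outcomes {12} sets them "before (week 0), during (week 4), and after the 8-week intervention (primary end-point, week 8"), and {18a} repeats the schedule. The Introduction's list for the basic version also refers to weekly self-assessments.
- **What is being tested.** Table 2 labels one factor "Factor 2: Mid-treatment phone call", with 150 of 300 participants at No. The text of {11a} describes it as an interview of roughly 20 to 30 minutes on goal fulfilment, a new 4-week goal and motivation. (Sequence generation {16a} numbers the two factors the other way round; Table 2's numbering is used here.)
- **Who knows the arm.** Under Implementation {16c}, "The study administrators will then assign the participants to the intervention groups in the digital platform according to the allocation sequence". Under {17a}, "There will be no blinding of participants, care providers, or assessors".
- **What the authors concede.** Section {11b} says that "all extra support given to a participant could be said to slightly alter the allocated interventions".

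**The concern.** A call about a late week-4 assessment lands at about week 5 of 8. That is when weekly module 5 asks participants to review progress and set a new goal, which is also the subject of the Factor 2 interview. The reminder call is listed as an adherence strategy, and encouragement to adhere is part of what the interview delivers. Nothing in the stated rule keeps the two apart. The enrolling administrators include clinical psychologists and psychology students with basic psychotherapy training, for whom a reminder could easily turn into encouragement.

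The word *may* is the weak point. Staff who know the allocation decide who is phoned, so the amount of extra contact can differ by arm, through differing lateness or differing inclination to call. If the less-guided arms receive more of it, the estimated benefit of guidance moves towards zero. The trial exists to decide which components to keep, and a diluted estimate could count against a useful one. Registering the time serves the clinician-time side of the incremental ratio in {20a}. It does not repair the drinking contrast on the other side of that ratio.

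**Working it through.** **1. The plan's own figure.** Sample size {14} gives 259 participants for a main effect of d = 0.35. Alpha and power are not stated in the article; two-sided 0.05 and 80% are assumed here. The normal approximation gives 2 × (1.960 + 0.842)² / 0.35² = 15.70 / 0.1225 = 128.2 per factor level, rounded up to 129, or 258 in total. A one-degree-of-freedom F test with N − 4 error degrees of freedom has power 0.7996 at N = 258 and 0.8012 at N = 259. So 259 is reproduced exactly, and the recruitment target of 300 gives 85.6%.

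**2. Effect of the reminder calls.** Let d be the interview's true effect, f the share of it that a reminder call carries, and p_no and p_yes the shares phoned at the No and Yes levels of Factor 2. Section {11c} does not restrict calls by arm, so both levels can be phoned. If effects add:

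- benefit at the Yes level: d + p_yes × f × d
- benefit at the No level: p_no × f × d
- observed contrast: d × [1 − f × (p_no − p_yes)]

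**3. Numbers.** The article gives none of f, p_no or p_yes, so the values below are assumptions.

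| p_no − p_yes | f | Dilution | Observed d | Power, N = 259 | Power, N = 300 |
|---|---|---|---|---|---|
| 0 | any | 0% | 0.350 | 80.1% | 85.6% |
| 0.30 − 0.20 = 0.10 | 0.10 | 1% | 0.35 × 0.99 = 0.347 | 79.3% | 84.9% |
| 0.10 | 0.25 | 2.5% | 0.35 × 0.975 = 0.341 | 78.1% | 83.8% |
| 0.10 | 0.50 | 5% | 0.35 × 0.95 = 0.333 | 76.0% | 81.9% |

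Dilution scales in proportion to the gap in call rates. If the Yes level were phoned more often, the sign would reverse and the effect would be inflated. The same reasoning applies to weekly written guidance, with its own f and call rates.

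**4. The week-8 primary rating.** Section {18b} says that if drinks per week are missing at week 8, they will be asked for in the telephone interview and used in place of the missing value. Sections {12} and {18a} schedule that interview without restriction by arm. Discretionary chasing therefore mainly affects whether a value comes from the platform or by telephone, and less whether there is a value at all.

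**The case against.** Four points can be made for the plan.

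- **The call is not the factor.** It is short, is made as a reminder, and happens only after a week's delay, whereas Factor 2 is a goal-setting interview. This stands: any contamination is partial, and the coincidence with module 5 is one of timing. Because weekly self-assessments may also trigger calls, they need not cluster at week 5.
- **The direction is not established.** More lateness without guidance is an inference. Half of the No level of Factor 2 (75 of 150) receives weekly written guidance and so does have a human prompt. This also stands.
- **Scripts and numbers of attempts belong in a manual.** That is fair for their absence from an article. But the article does state the rule, and it states it as discretionary for staff who are not blinded. That is a choice made in the text, not an omission.
- **The plan acknowledges extra support and registers the time.** That allows cost accounting and a description by arm; it does not prevent unequal contact.

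Two stronger readings may tempt a reader. The first takes dilution as p_no × f alone: 0.40 × 0.5 = 0.20, so d = 0.35 × 0.80 = 0.28 and power 61.2% at N = 259 or 67.6% at N = 300. This requires reminder calls to have no effect at the Yes level, although the rule is open to all arms, and nothing in the article supports 40% phoned or half the interview's effect. The second is that completeness of the primary outcome would depend on arm. Section {18b} provides a route for recovering missing values that does not rest on the reminder-call discretion, so only a possible arm difference in platform versus telephone rating remains.

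**Conclusion.** The point holds as a modest weakness that is cheap to remove. The rule in {11c} lets staff who know the allocation decide on human contact during treatment, in a trial that tests human contact, and registering the time does not remove that contact. The size is f × (p_no − p_yes): zero if call rates are equal, and 2.5% to 5% at assumed rates of 30% against 20% with f between 0.25 and 0.5. At N = 259 that costs about 2 to 4 points of power (80.1% to 78.1% or 76.0%). These figures rest on additive effects, an assumed alpha and power, and call rates and f that the article does not give. The documents do not support a claim of serious dilution or of arm-dependent loss of the week-8 outcome.

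**What to change.** In {11c}, replace *may* with one rule applied identically in all four arms: the same trigger day after the due date and the same number of attempts for every late participant. Limit the call to a script that asks for the survey, with no discussion of goals, progress or motivation. Report the number of reminder calls by arm, and the number of week-8 primary values obtained by platform and by telephone in each arm.

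The cost is a sentence or two in the protocol, a short script and one descriptive table. The article's version is dated June 2023 and expects recruitment until Q4 2024, so a change made during that period would still cover later participants.

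Relying on automated reminders alone for the week-4 assessment is optional. It would remove the overlap with the mid-treatment interview for that assessment, but would probably lose some week-4 data. The mixed model in {20a} uses all measurement points, and {22} measures adverse effects at week 4, so this is a real trade-off. Safety contacts under {11b} are unaffected by any of these changes.
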